**Genotype 6 and SOF/DCV**

The programme of ALLY trials only included one patient with genotype 6 infection; this patient was in the post-transplant cohort of the ALLY-1 trials [[7](#_ENREF_7)]. This patient achieved SVR12 with 12 weeks of SOF/DCV and ribavirin. The French Compassionate Use Programme enrolled 5 genotype 6 patients with advanced liver fibrosis. Patients were treated with 24 weeks of SOF/DCV with ribavirin added at the physician’s discretion. 3/5 patients had cirrhosis and 5/5 achieved SVR12 (Bristol Myers Squibb, personal communication). As such whilst SOF/DCV is recommended as an option for treatment for genotype 6 in clinical guidelines [[8](#_ENREF_8)], there is no specification made for duration of therapy.

Real-world data is emerging: recent data of SOF/DCV in genotype-6 shows high cure rates [[9](#_ENREF_9)]. 120/127 (94%) genotype-6 patients achieved SVR12 with 12 weeks of treatment. Cure rates were 92% (52/59) with 12 weeks’ treatment even in the hardest to treatment population with cirrhosis.

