**SOF/DCV treatment for less than 12 weeks**

There are very limited data on the efficacy of SOF/DCV at durations less than 12 weeks. The largest study to date is the ALLY-2 trial [[10](#_ENREF_10)] limited to the treatment of HIV/HCV co-infected individuals and for this reason HIV co-infected patients are not included in stratum A. 76% (31 of 41) of individuals with genotype 1 infection receiving a shortened duration of therapy (8 weeks; not selected based on treatment response or baseline characteristics) achieved SVR12. The question addressed within this protocol is whether early on treatment responses can be used to increase cure rates with shortened therapy.

There is one study to date of response guided therapy published with sofosbuvir/daclatasvir [[11](#_ENREF_11)]. Treatment was shortened from 12 to 8 weeks in an Egyptian genotype 4 population when viral load was undetectable at day 14. The shortening strategy was found to be non-inferior to the standard of care. There are no studies seekinn to identify patient groups who may be cured with less than 8 weeks of therapy with sofosbuvir/daclatasvir. However, one study from Lau et al [[12](#_ENREF_12)] in a highly selected population genotype 1b, female, with low BMI, found 100% cure rate (18/18) with 3 weeks of triple-drug combination treatment (not SOF/DCV) for those patients with a rapid virological response (<500 IU/ml at 48h). The hypothesis tested in this trial is that those patients responding in a similar way to SOF/DCV will be cured with shortened therapy. Whilst the Lau et al paper suggests high cure rates may be achieved with 3 weeks of therapy, a four week duration will be used in this study to provide greater chance of successful treatment.

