For both treatment strata, the target cure rate is 90%, with an unacceptably low cure rate of 70% (final lower 95% CI limit should exceed this). Assuming 90% power and one-sided alpha=0.05, requires 37 participants to exclude the null hypothesis (cure <90%). Assuming 5% loss to follow-up in both strata, and that 65% (based on [[12](#_ENREF_12)]) and 90% achieve on-treatment response and receive shortened therapy in Stratum A and B respectively, 60 participants would be required in Stratum A (pooling genotypes), and 43 in Stratum B. 5% loss follow-up is consistent with experience in the local setting which has generally followed patients for much longer than 12 weeks post end of treatment as here [personal communication, OUCRU].

- 1. Analysis Plan (Brief)

The analyses will be described in detail in a full Statistical Analysis Plan. This section summarises the main issues.

The primary analysis would be intention-to-treat, including all participants regardless of treatment received. Primary analysis of SVR12 (the primary endpoint) would be as observed (those not meeting the formal “failure” definition but discontinuing first-line treatment early and not undergoing re-treatment with detectable HCV RNA 12 weeks later counted as not achieving the primary endpoint). Any missing data at 12 weeks post EOT due to assay failure or missed visit would be multiply imputed within stratum based on all viral load measurements and baseline characteristics, using chained estimating equations. Continuous variables would be transformed for normality, and data augmented following standard recommendations to avoid problems with perfect prediction. The distribution of imputed data would be checked versus observed data.

Secondary analyses for each outcome would be based on a per-protocol population, which we (arbitrarily) define as receiving >90% and <110% of the prescribed duration of first-line treatment. Assessment of treatment received will be based on both prescription and self-reported adherence.

A further secondary analysis will exclude reinfections leading to rebound virus, with reinfection determined by genotype and full genome sequencing.

As the duration of follow-up is relatively short, primary analysis would consider outcomes as binary. Proportions and their 95% CI would be estimated using Poisson regression.

1. Data management
   1. source data

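### Section 9.1 names the 90% target as the null; 37 participants fits a 70% null at one-sided 5%, which does not match a conventional 95% CI success rule

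*Protocol*

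**What the plan says.** Protocol section 9.1 (Sample Size justification) makes three statements in two sentences.

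- The target: "For both treatment strata, the target cure rate is 90" per cent.
- The floor and the success rule: "with an unacceptably low cure rate of 70% (final lower 95% CI limit should exceed this").
- The size and its purpose: "Assuming 90% power and one-sided alpha=0.05, requires 37 participants to exclude the null hypothesis (cure <90" per cent).

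The same section inflates 37 to 60 in Stratum A and 43 in Stratum B, for 5% loss to follow-up and for the shares expected to receive the shorter course (65% and 90%). Section 9.2 plans 95% confidence intervals for proportions from Poisson regression. It does not say which variance is used. Neither section says whether the 95% interval is one-sided or two-sided.

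**The concern.** The value to be excluded should be the unacceptable rate, not the rate hoped for. As printed, the second sentence asks the trial to rule out values below its own target, which contradicts the sentence before it.

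There is also a mismatch of error rates. A one-sided 5% test corresponds to a one-sided 95% limit, or to the lower end of a two-sided 90% interval. The lower end of a conventional 95% interval is a one-sided 2.5% test. With 37 participants this moves the number of cures that counts as success.

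The null, the error rate and the threshold together define what the trial may conclude about shortened treatment. A result on the boundary could be read either way after the data are seen.

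**Working it through.** **Inputs (section 9.1):** p1 = 0.90, p0 = 0.70, one-sided alpha 0.05, power 90%, n = 37, loss 5%, short-course share 65% (Stratum A) and 90% (Stratum B).

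**1. Reproduce 37.** Take the smallest k with P(X ≥ k | n, 0.70) ≤ 0.05; power is P(X ≥ k | n, 0.90), with X binomial.
- At n = 37, P(X ≥ 30 | 0.70) = 0.0947 is too large and P(X ≥ 31 | 0.70) = 0.0440 passes, so k = 31.
- Power is P(X ≥ 31 | 0.90) = 0.929.
- No smaller n reaches 90%.

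So 37 is right for a 70% null at one-sided 5%.

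**2. Reproduce the inflation.** 37/(0.95 × 0.65) = 59.9, giving 60. 37/(0.95 × 0.90) = 43.3, stated as 43. The second is rounded down: 43 × 0.855 = 36.8 expected, a shortfall of 0.2 of a participant, which is trivial.

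**3. Test the null as printed (cure <90%).** With 37/37 the two-sided 95% exact lower limit is 0.025^(1/37) = 0.905, above 0.90. With 36/37 it is 0.858, and even the one-sided 95% limit is 0.878. Only 37/37 would exclude the null. If the true cure rate is 90%, that has probability 0.90^37 = 0.020. No test can have 90% power when the alternative lies on the boundary of the null.

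**4. Apply the success rule as a two-sided 95% CI, n = 37.**

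| Cures | Exact lower limit | Wilson lower limit | Above 0.70? |
|---|---|---|---|
| 31 | 0.680 | 0.689 | no |
| 32 | 0.712 | 0.720 | yes |

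The cut-off is 32/37. Size is P(X ≥ 32 | 0.70) = 0.0172 and power is P(X ≥ 32 | 0.90) = 0.840.

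**5. Apply the Poisson interval named in section 9.2, two-sided 95%.** The lower limit is p × exp(−1.96 × SE), where SE is the standard error of log p.
- Robust variance, SE = √[(1 − p)/(np)]. At 31/37: 0.838 × exp(−1.96 × 0.0723) = 0.727, which passes. At 30/37 it is 0.694, which fails. The cut-off is 31/37, power 92.9%, actual one-sided error 4.4% instead of the nominal 2.5%.
- Model-based variance, SE = 1/√k. At 36/37: 0.973 × exp(−1.96/6) = 0.702, which passes. At 35/37 it is 0.679, which fails. The cut-off is 36/37, power 10.4%.

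**6. Check the alternative of a one-sided 95% limit.** The exact one-sided 95% lower limit at 31/37 is 0.705, so 31/37 passes and the section 9.1 figures hold (size 4.4%, power 92.9%). The method still matters: a robust-variance Poisson 90% interval at 30/37 gives 0.811 × exp(−1.645 × 0.0794) = 0.712, which passes with size 9.5%.

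**The case against.** **The null is only a slip of wording.** This is largely right. The 70% floor stands in the preceding sentence, and 37 was plainly computed against it. A reader might infer that the trial was sized against the wrong null; the arithmetic shows that it was not. The printed statement still needs correcting.

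**The 95% limit may be one-sided.** The words "final lower 95% CI limit should exceed this" are followed at once by a one-sided 5% alpha, and on that reading the two sentences agree with 92.9% power. This stands as a possible reading. The protocol does not state it, and section 9.2 uses the ordinary term for a two-sided interval.

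**The interval method can be left to the analysis plan.** Fair as to detail. But section 9.1 already fixes a success rule, and its power runs from about 10% to 92.9% depending on the method. It is therefore not enough to say without qualification that power is 84%.

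**The primary analysis includes everyone.** Section 9.2 specifies intention-to-treat. Applied to all 60 in Stratum A, the exact two-sided rule needs 50/60 and has power 96.6%; applied to all 43 in Stratum B it needs 37/43 and has 86.7%. The sizing sentence counts only short-course participants, so 84% refers to the 37 that section 9.1 itself counts.

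**The planning rates look soft.** A reader might go further and cite the background section, where "Cure rates were 92% (52/59") does not agree with itself: 52/59 = 88.1%, whereas 54/59 = 91.5%. The documents do not show which figure is misprinted, section 9.1 does not use it as an input, and it is not the only genotype 6 cirrhosis result given. Likewise the 65% response rate comes from a study "in a highly selected population genotype 1b, female, with low BMI", but the protocol says so openly and gives no other rate. Neither supports a lower power figure.

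**Conclusion.** The point holds, as an error of statement and an unresolved success rule. The null as printed is wrong on any reading. The one-sided 5% alpha and a conventional two-sided 95% CI are different tests: at 37 evaluable participants the cut-off moves from 31 to 32, size from 4.4% to 1.7%, and power from 92.9% to 84.0%. A result of 31/37 is a success under one and a failure under the other.

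The 84.0% assumes a two-sided 95% interval by an exact or Wilson method, a true cure rate of 90%, and 37 evaluable participants. A one-sided 95% exact limit or a robust-variance Poisson 95% interval keeps 92.9%; a model-based Poisson interval leaves about 10%. The documents do not support saying that the trial is underpowered as such, or that its recruitment targets are wrong.

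**What to change.** In section 9.1, state the hypotheses as H0: cure ≤70% and H1: cure 90%. Then choose one success rule and carry it into section 9.2 and the analysis plan, before any outcome data are reviewed:

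- **(a)** Success is a one-sided 95% lower limit (the lower end of a two-sided 90% CI) above 70%, by an exact method. This keeps 37 participants and at least 90% power (31/37, power 92.9%).
- **(b)** Success is the lower end of a two-sided 95% CI above 70%, by an exact or Wilson method. Restate power as about 84% at 37 evaluable participants (32/37).

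Under either option, name the interval that decides success. If Poisson regression is kept for reporting, state its variance and say that it does not decide success. Separately, check the 92% and the 52/59 in the background against their source and reconcile them.

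The cost is wording in the protocol and the analysis plan. Option (b) lowers the stated power. Neither option needs more participants.

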**STRATUM B (compensated cirrhosis, G6 HCV only, Response guided therapy)**

All participants will receive a minimum of 12 weeks of treatment. Those participants who have achieved virological suppression (VL <500IU/ml, as measured by Cobas assay, Roche) at the time of their D14 visit or sooner after treatment initiation will complete therapy at 12 weeks. Those who do not achieve virological suppression will continue to complete 24 weeks of therapy.

- 1. Protocol Treatment Discontinuation

In consenting to the trial, participants are consenting to trial treatment, trial follow-up and data collection.

Treatment (or retreatment) will be discontinued if any of the following occurs:

- toxicity which the investigator considers impedes the ability of the patient to continue intervention and/or the product information for the drug(s) contains a directive on discontinuation in the event of this specific toxicity
- participant requests for any reason to withdraw consent for treatment
- virological failure as defined above (move to retreatment if first-line failure and mild disease)

However, any such patient discontinuing study treatment (or retreatment) will be invited to continue follow-up “off study drug, on study” in order to obtain data on overall cure and adverse events. Participants should only discontinue study follow-up if they explicitly withdraw consent to continue to attend study visits. In this situation, participants may still contribute data collected at their routine clinic visits to the trial, providing they are willing to do so (“off study, follow-up through medical records only”).

1. Assessments & Follow-up
   1. Trial Assessment Schedule

See Appendix II, Trial Assessment Schedule.

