**7.2.5.E Missed doses**

If a dose is missed and it is within 18 hours of the normal time, participants should be instructed to take the tablet as soon as possible and then participants should take the next dose at the usual time. If it is after 18 hours then participants should be instructed to wait and take the next dose at the usual time. Participants should be instructed **not to** take a double dose. Any doses missed during the treatment course should be taken at the end of the prescribed course.

- 1. DACLATASVIR (DCV)
     1. **PRODUCT**

The product is daclatasvir 60mg taken once a day, swallowed whole and not chewed (bitter taste). Although food does not affect the absorption of DCV, it will be taken with SOF, so they must both be taken with food.

**Side-effects:** see above Table.

- - 1. **TREATMENT SCHEDULE**

The duration of DCV therapy will be determined by the Stratum the participant is in, and their response on therapy (see study schema).

- - 1. **DISPENSING**

The trial or clinic nurse will dispense DCV (and SOF) after taking the completed prescription form to the site pharmacy. All participants will receive a 28-day supply at Day 0. Further supplies will provided at Day 28 dependent on response to therapy on Day 2 (mild disease) or Day 14 (cirrhosis). On no account should any drug assigned to a participant be used by anyone else. Unused drug must be returned to the site pharmacy immediately if a participant withdraws from treatment.

All drug dispensed at and returned to the site pharmacy should be documented on a site Accountability Log, maintained by a named person (trial pharmacist or research nurse). The designated trial pharmacist/nurse will, on receipt of supplies prior to the commencement of the trial, conduct an inventory and complete a receipt. Inventories will be conducted monthly, and logs returned to OUCRU CTU. Procedures for drug shipping, labelling, accountability, temperature monitoring and destruction will be detailed in the trial’s SOPs. OUCRU CTU will monitor drug accountability at site visits. There is no requirement for temperature monitoring of treatment packs after they are dispensed from pharmacy.

- - 1. **DRUG-DRUG INTERACTIONS**

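### The secondary per-protocol rule (Section 9.2) excludes participants whom the protocol itself stops for virological failure, and applies to safety outcomes those who stopped early for toxicity cannot enter

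*Protocol*

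**What the plan says.** Section 9.2 makes the primary analysis intention-to-treat in all participants. It then adds: "Secondary analyses for each outcome would be based on a per-protocol population". Membership of that set rests on a single criterion of treatment received: "which we (arbitrarily) define as receiving >90% and <110% of the prescribed duration of first-line treatment". Treatment received is to be judged from prescription and self-report. The text does not say whether duration means calendar days or doses.

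Section 5.2 lists events at which treatment is discontinued. One is toxicity that prevents the participant from continuing. Another is "virological failure as defined above (move to retreatment if first-line failure and mild disease".

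Sections 7.2.5.E and 7.3.5.G both instruct: "Any doses missed during the treatment course should be taken at the end of the prescribed course".

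Section 2.2 makes protocol-defined failure part of the primary endpoint. It also lists, as a secondary endpoint, adverse events that led to a change in the study drugs or any other medication.

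**The concern.** A per-protocol set should hold those who were treated as the protocol directs. Under Section 5.2, stopping at virological failure is what the protocol directs. The duration rule nevertheless treats that stop as a departure, so membership depends on the outcome being measured. These participants are non-cures by definition, so losing them moves per-protocol SVR12 after first treatment in one direction only.

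The same rule covers safety. A participant who stops both drugs early for toxicity has the event that the treatment-change endpoint counts, and is removed from that endpoint's per-protocol analysis because of it. Section 7.7 regards non-adherence caused by intolerance or toxicity as part of the strategy under evaluation, so a safety result without it is hard to interpret.

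At stake is whether agreement between the per-protocol and primary results tells the reader anything.

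**Working it through.** **The plan's own figures (Section 9.1).** Inputs: "For both treatment strata, the target cure rate is 90%, with an unacceptably low cure rate of 70"%; "Assuming 90% power and one-sided alpha=0.05, requires 37 participants to exclude the null hypothesis"; "Assuming 5% loss to follow-up in both strata"; and shortened therapy in 65% of Stratum A and 90% of Stratum B ("90% achieve on-treatment response and receive shortened therapy in Stratum A and B respectively").

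- Exact single-arm binomial test of 0.70 against 0.90, n = 37, success at 31 or more cures: one-sided alpha 0.044, power 0.929. The 37 is reproduced.
- Stratum A: 37 / 0.95 / 0.65 = 59.9, stated as 60. Stratum B: 37 / 0.95 / 0.90 = 43.3, stated as 43.

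**Who leaves the set at the lower limit.** With a prescribed course of D days (Section 5.1: 4, 8, 12 or 24 weeks), membership needs more than 0.9 × D.

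| D | 0.9 × D | Fewest days to stay in | 1.1 × D | Made-up doses that exceed the upper limit, if calendar days are counted |
|---|---|---|---|---|
| 28 | 25.2 | 26 | 30.8 | 3 |
| 56 | 50.4 | 51 | 61.6 | 6 |
| 84 | 75.6 | 76 | 92.4 | 9 |
| 168 | 151.2 | 152 | 184.8 | 17 |

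Anyone stopped for failure or toxicity before the third column's figure is excluded.

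**Direction for SVR12.** With c cures among n, excluding k non-cures changes c/n to c/(n − k), which is larger whenever c and k are above zero.

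**Size, with assumed counts.** The documents give no rate of on-treatment failure, so k = 1, 2, 3 is a range and not an estimate.

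- From 33/37 = 89.2%: 33/36 = 91.7%, 33/35 = 94.3%, 33/34 = 97.1%. The gain is 2.5 to 7.9 points.
- From 54/60 = 90.0%: 54/59 = 91.5%, 54/58 = 93.1%, 54/57 = 94.7%. The gain is 1.5 to 4.7 points.

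Against the 70% bar, using exact (Clopper-Pearson) one-sided 95% lower limits to match the stated alpha: 30/37 = 81.1% has lower limit 67.4%; 30/35 = 85.7% has lower limit 72.3%. Exclusion alone crosses the bar.

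**Safety, with an assumed count.** If 3 of 103 participants stop early for toxicity and no other treatment-changing events occur, the endpoint is 3/103 = 2.9% in all participants and 0/100 per protocol.

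**Made-up doses.** Counted in calendar days, a 28-day course with three doses made up ends on day 31, and 31/28 = 110.7%, so the participant is excluded. Counted in doses, 28/28 = 100%, and the participant stays in.

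**The case against.** The strongest reply is that little rides on this. The analysis is secondary, the protocol calls its cut-offs arbitrary, and nothing makes the per-protocol result a criterion for the conclusion. That stands, and it limits the point to one secondary analysis.

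On-treatment failure may also be rare, above all in the 4-week group, who were below 500 IU/ml at 48 hours. Failure needs two measurements at least a week apart. To be excluded from a 28-day course a participant must stop by day 25, so the first qualifying value must fall by day 25 − 7 = 18. Section 5.1 looks for rebound mainly after treatment, and relapses after a completed course stay in the set as failures. A reader might infer that most virological failures would be dropped; the documents do not support that.

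Three other stronger readings fail.

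- **Made-up doses overstate cure.** Exclusion arises only under a calendar-day count, which the text neither states nor rules out. It also has no fixed direction: from 33/37, removing three cured participants gives 30/34 = 88.2%, and removing three non-cured gives 33/34 = 97.1%. Participants who stopped for toxicity but were cured would likewise lower the per-protocol rate when removed.
- **Any plausible result flips at the 70% bar.** The crossing depends on the counts and the interval. For 31/37 the two-sided exact lower limit is 68.0% and the one-sided limit is 70.5%, so at the stated alpha it already passes. For 30/37 and 30/35 the two-sided exact limits are 64.8% and 69.7%, so two exclusions do not cross; three do (30/34, 72.6%). Section 9.2 names Poisson regression, not exact limits.
- **Treatment-changing events vanish from the safety results.** The endpoint includes changes to other medication, and short interruptions need not breach 90%. Only participants whose early stop takes them to 90% or less are lost.

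It may also be said that detail belongs in the statistical analysis plan, which is not at hand. But the protocol itself fixes both thresholds and the scope, and a plan that followed it would carry the problem forward.

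**Conclusion.** The point holds in limited form. As worded, the per-protocol rule conflicts with Section 5.2: it removes participants who followed the protocol and failed on treatment, which can only raise per-protocol SVR12 after first treatment. It also removes early toxicity stops from a safety endpoint meant to count them. The direction for virological-failure stops follows from the definitions. The size does not: the gains of 1.5 to 7.9 points, the 67.4% to 72.3% example and the 2.9% to 0 example all rest on assumed counts.

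A reader might conclude that the trial's cure or harm results are biased. They are not on this account, because the primary analysis keeps everyone. What is weakened is the per-protocol analysis as a check on the primary one. The treatment of made-up doses is an ambiguity to settle, not a demonstrated error.

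**What to change.** Define the per-protocol set as participants who either took more than 90% and less than 110% of the prescribed first-line doses, or stopped early because of protocol-defined virological failure, the latter retained as failures. Count doses taken, so that doses made up as instructed exclude no one. Keep the upper limit: without it, someone treated well beyond a shortened course would count as per protocol. Use the set for efficacy outcomes only, and analyse all safety outcomes in everyone who took at least one dose.

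The cost is two sentences in the protocol or analysis plan. Section 7.7 already collects pill counts and self-report, and no treatment rule changes. The one downside is a per-protocol cure rate that may be slightly less favourable.

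### Poisson regression is a poor source for the 95% CI that decides the 70% cure criterion: far too wide with model-based variance, and still worse than a binomial interval with robust variance

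*Protocol*

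**What the plan says.** Section 9.1 sets a target cure rate of 90% and an unacceptable rate of 70% in each stratum, and makes the 70% a decision rule: "final lower 95% CI limit should exceed this". The sizing reads: "Assuming 90% power and one-sided alpha=0.05, requires 37 participants". After allowing for loss to follow-up and for the share who receive shortened therapy, "60 participants would be required in Stratum A (pooling genotypes), and 43 in Stratum B".

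Section 9.2 makes the primary analysis intention-to-treat on everyone enrolled, treats the outcome as binary, and multiply imputes missing 12-week results. On estimation it says: "Proportions and their 95% CI would be estimated using Poisson regression". It gives neither a link function nor a variance estimator, and leaves detail to a full SAP, which is not available here.

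**The concern.** A Poisson model takes the variance to equal the mean. For a proportion p this replaces p(1-p)/n by p/n. The difference is small when events are rare and large when p is near 0.9, as planned here. Because the trial's verdict in each stratum is the position of the lower limit relative to 70%, the width of the interval decides the conclusion. If it is three times too wide, a strategy that meets its 90% target would usually be reported as not excluding 70%, and the published interval would run past 100%. If it is too narrow, the rule passes too easily. The sentence allows either.

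**Working it through.** **Inputs (section 9.1).** Target 0.90; unacceptable rate 0.70; rule: lower 95% limit above 0.70; one-sided alpha 0.05; power 90%; 37 evaluable participants; strata of 60 and 43.

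**The plan's own figure.** With n=37 and success defined as at least 31 cures, the exact binomial gives P(X≥31 | 0.70) = 0.044 and P(X≥31 | 0.90) = 0.929. With n from 33 to 36, the exact rule at alpha 0.05 reaches power of only 0.855 to 0.894. So 37 reproduces. Enrolment: 37/(0.95 × 0.65) = 59.9, stated as 60; 37/(0.95 × 0.90) = 43.3, stated as 43.

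**Interval formulas (log link assumed; x cures out of n, p = x/n).**
- Poisson, model-based: p × exp(±1.96/√x)
- Poisson, robust (sandwich): p × exp(±1.96 × √((1−p)/x))

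The ratio of the two standard errors is 1/√(1−p), which is 1/√0.1 = 3.16 at p = 0.9.

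**Example, 33/37 (89.2%).**
- Model-based: SE = 1/√33 = 0.174, limits 63.4% to 125.5%.
- Robust: SE = √(0.108/33) = 0.057, limits 79.7% to 99.8%.
- Clopper-Pearson: 74.6% to 97.0%.

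**Decision rule.** For each method, take the smallest x whose lower two-sided 95% limit exceeds 0.70. The exact binomial then gives the chance of reaching it at 0.90 (power) and at 0.70 (one-sided error).

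| n | Method | Cures needed | Power | One-sided error |
|---|---|---|---|---|
| 37 | Poisson, model-based | 36 | 10.4% | <0.1% |
| 37 | Poisson, robust | 31 | 92.9% | 4.4% |
| 37 | Wilson or exact | 32 | 84.0% | 1.7% |
| 43 | Poisson, model-based | 41 | 18.2% | <0.1% |
| 43 | Poisson, robust | 35 | 97.6% | 6.7% |
| 43 | Wilson / exact | 36 / 37 | 93.9% / 86.7% | 3.1% / 1.3% |
| 60 | Poisson, model-based | 55 | 43.7% | <0.1% |
| 60 | Poisson, robust | 48 | 99.4% | 5.7% |
| 60 | Wilson / exact | 49 / 50 | 98.5% / 96.6% | 3.0% / 1.4% |

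Under model-based variance the failure rates at a true 90% are therefore 89.6%, 81.8% and 56.3%. At n=37, 36 cures give a lower limit of 70.2% and 35 give 67.9%. At n=60, 54 cures, exactly 90%, give 68.9% and fail. An identity link would be stricter still at n=37: even 37/37 gives 1 − 1.96/√37 = 0.678.

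**Quality of the intervals at n=37 and a true 90%.**
- Model-based: the upper limit exceeds 100% in practically every trial.
- Robust: coverage of the nominal 95% interval is about 89%. The upper limit exceeds 100% whenever 34 to 36 are cured, about 47% of trials. At 37/37 the standard error is zero and the interval is 100% to 100%.

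**How much hangs on the unstated option.** At n=37, any count from 31 to 35 succeeds with robust variance and fails with model-based variance. At a true 90% that has probability 0.929 − 0.104 = 0.825.

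**The case against.** The best defence is that the protocol never says the model-based variance will be used. Poisson regression with robust variance is a recognised method for binary outcomes and fits the sentence equally well. The section is headed as brief, and a variance estimator is the kind of detail a SAP supplies. This stands: the silence about the variance is not in itself the finding. A reader might infer that the planned rule will fail about 90% of the time. The documents do not support that as a general statement, since it needs the model-based default and n=37, while the primary analysis covers whole strata.

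It is also tempting to say that robust Poisson is too lenient at n=37 because 4.4% exceeds 2.5%. That does not hold either. The protocol states a one-sided alpha of 0.05, and the robust rule of 31/37 is the exact design rule that gives 37.

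The 37/37 case has probability 0.9^37, about 2%, and does not change the pass decision. And the replacement costs power at n=37.

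The defence does not rescue the named method. Even on its favourable reading, coverage at n=37 is well below 95%, impossible upper limits are common, and one-sided error exceeds the stated 5% at both whole-stratum sizes.

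**Conclusion.** The concern holds as a criticism of the method the protocol names, whichever variance is intended. With model-based variance the 70% rule is close to unusable: power at the 90% target is 10% at n=37, 18% at n=43 and 44% at n=60, against 90% planned. That error is toward missed success; false success is practically excluded. With robust variance the decision rule works at n=37, but the interval under-covers there, often passes 100%, and gives one-sided error of 6.7% and 5.7% on the whole strata.

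These figures assume a log link, a two-sided 95% interval, complete outcomes and a common true cure rate. They are given at 37, 43 and 60 because section 9.1 sizes on those receiving shortened therapy while section 9.2 analyses everyone. With a 90% two-sided interval, whose lower limit is the one-sided 95% limit, the model-based rule at n=37 still fails 73% of the time. The SAP may settle the variance, but a robust choice there would leave the remaining defects.

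**What to change.** Replace the Poisson sentence in section 9.2, and carry the change into the SAP: proportions and 95% CIs by Wilson or exact (Clopper-Pearson) limits; after multiple imputation, a Wilson or logit-scale interval pooled by Rubin's rules; the 70% criterion applied to that same interval.

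It needs no new data or participants, but it has a cost in power that should be stated. With a two-sided 95% interval at n=37 the rule becomes at least 32/37 and power is 84%, not 90%. There are two ways to deal with this:

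- Keep the two-sided 95% limit and restate the power as 84% at n=37.
- Read the criterion from the one-sided 95% limit, which matches the stated one-sided alpha of 0.05. The exact limit then needs 31/37 (power 92.9%, error 4.4%), 36/43 (93.9%, 3.1%) or 49/60 (98.5%, 3.0%). Wilson gives the same rules at 37 and 43 but 48/60 at n=60, with error 5.7%, so the exact limit is the safer choice under this option.

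Either way, section 9.1 should say which limit the criterion uses.
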